### 3. Inclusion and Exclusion Criteria

*List the inclusion/exclusion criteria:*

A total of 375 African American mother-infant dyads will be recruited from AU's newborn nursery. Co-participation of the mother-infant dyad is a study requirement. Paternal involvement is voluntary, but not necessary. If fathers are interested in participating, they will sign separate consents.

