### Demographics and Health

*Family demographics and maternal/infant health.* Parent and demographic covariates will include: Pre-pregnancy BMI, smoking during pregnancy, gestational weight gain, maternal type 2 or gestational diabetes mellitus, maternal and paternal BMI assessed at the first research visit, income, education, and employment (work status, hours worked). Infant covariates will include: Infant weight at age 1 week (the first assessment) adjusted for gestational age, child sex, and feeding mode (predominantly breastfed if 80% or more of milk feedings were breastmilk, predominantly formula-fed if 80% or more of milk feedings with formula milk, or mixed-feedings).

*Parent weight and height.* Mothers' pre-pregnancy weight and weight prior to delivery will be obtained from chart abstraction, if available. Should these data be missing from charts, it will be collected via survey. Mother's height will be measured using stadiometer at AU and weight will be measured using a calibrated scale at AU. At all subsequent visits, mothers and fathers will again be weighed using calibrated scales.

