First, we will examine differences in BMI and other weight outcomes at 16 weeks between the Sleep SAAF group and the control group using a linear mixed-effects model. The linear mixed-effects model will include intervention group and infant weight at age 1 week adjusted for gestational age. These analyses will test whether the Sleep SAAF group and the control group differ in their weight outcomes at age 16 weeks, which has previously been linked to child obesity risk at age 2 years.

Next, we will consider growth models that examine rate of change in weight from birth to 16 weeks. We will conduct growth curve analyses using hierarchical linear modeling to test whether the Sleep SAAF and control groups differ in their rate of change in weight over time. The model will include intervention group, time of growth measure, and infant weight adjusted for gestational age. These analyses will evaluate whether the Sleep SAAF group shows less of an increase in weight over time compared to the safety control group.

As an additional test of rapid weight gain, weight gain z-scores will be calculated for each measurement subsequent to the first intervention session at age 3 weeks (8 weeks and 16 weeks). Rapid weight gain scores will be calculated as an increase in weight-for-

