
|                                                                                                                                                                                                                                                                                                                                                                                                                                                                                                                                                                                                                                                                                                                                                       |                                 |
|-------------------------------------------------------------------------------------------------------------------------------------------------------------------------------------------------------------------------------------------------------------------------------------------------------------------------------------------------------------------------------------------------------------------------------------------------------------------------------------------------------------------------------------------------------------------------------------------------------------------------------------------------------------------------------------------------------------------------------------------------------|---------------------------------|
| 
The primary outcomes for this study will be BMI z scores at 16 weeks (Specific Aim 1) and parent and infant behaviors at 8 weeks and 16 weeks (Specific Aim 2). We used G Power 3.1.9.2 to estimate the smallest intervention effect size we can detect with 80% power, a 5% two-tailed Type 1 error rate, and two groups of 175 each (conservatively assuming 10% attrition over the course of the study). We can achieve 80% power with an effect size <math>d</math> of 0.34. Our recent research showed an effect size of approximately 0.4 for infant nighttime sleep duration at 8 weeks and for infant conditional weight gain at 6 months, suggesting that we will have sufficient power in our sample to detect intervention effects.
 |                                 |

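### On its natural reading, the Aim 1 growth-curve model gives its rate test no baseline adjustment, which costs precision that the weights already collected could recover

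*Supplement*

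**What the plan says.** All references are to the latest protocol version in the Supplement.

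- **Growth-curve model (7.a, Specific Aim 1).** It examines "rate of change in weight from birth to 16 weeks" by hierarchical linear modelling, to test whether the arms differ in rate of change. Its content is given as: "The model will include intervention group, time of growth measure, and infant weight adjusted for gestational age". The sentence does not give the age of that weight, the measurements that form the outcome series, or any interaction term. Arm-by-time is only implied by the stated purpose.
- **16-week model (7.a, preceding paragraph).** It adjusts explicitly for weight at age 1 week.
- **Covariate list (6.a, Demographics and Health).** It defines the infant covariate as "Infant weight at age 1 week (the first assessment) adjusted for gestational age".
- **Available weights (6.a).** Weight is measured in the nursery at enrolment and at home visits at 1, 3, 8 and 16 weeks. Randomisation is at Home Visit 1, 7-10 days after birth. The first programme session is at 3 weeks.
- **Power (7.b).** The calculation names BMI z at 16 weeks as the Aim 1 outcome. No figure is given for the growth-curve slope.

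**The concern.** A covariate in the level of a growth curve shifts each infant's whole curve up or down and says nothing about its steepness. If the sentence is implemented as listed, with arm-by-time added because the aim needs it, the rate comparison is the unadjusted one even though the plan appears to adjust for early weight. If the covariate is the birth or 1-week weight and the outcomes run from birth, the same measurement also stands on both sides of the model.

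What is at stake is the precision of one of the Aim 1 tests of slower weight gain. Infants who start heavy tend to drift down relative to the reference, as the protocol itself expects (section 8, expected rates for the screening criteria, citing regression to the mean). Early weight and subsequent slope are then negatively correlated, and a slope comparison that ignores this has a larger standard error than the same data allow.

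**Working it through.** **The plan's own figure.** Section 7.b states "We can achieve 80% power with an effect size d of 0.34" for 175 per arm with 10% attrition. A two-sample t-test on 175 × 0.9 = 157.5 per arm gives a detectable d of 0.317, and 85% power at 0.34. The stated value is not reproduced (135 per arm gives 0.342), but the mismatch is conservative and separate from this point. Only the roughly 157 evaluable infants per arm are used below.

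**Why the level term does nothing.** Fit a line to each infant. The model is then two regressions, one for the intercepts and one for the slopes. As listed, the slope regression contains (1, arm) and the intercept regression contains (1, arm, early weight). When one equation's regressors are a subset of the other's, joint estimation leaves the smaller equation at ordinary least squares. The arm-by-time estimate is therefore the plain difference in mean slopes. This holds for any level-only covariate, whether or not it lies on the curve.

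**Why a common baseline mean helps.** Dropping arm from the intercept equation lets the intercept-slope correlation ρ work. The variance of the rate difference is multiplied by 1 − ρ², so the excess variance as listed is 1/(1 − ρ²) − 1.

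**Z-score scale (assumed).** Visits are at 0, 1, 3, 8 and 16 weeks, with time in units of 16 weeks. Total SD is 1, measurement variance is 0.1, and r is the correlation between birth and 16-week values.

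- True part: intercept variance 0.9, covariance r − 0.9, slope variance 1.8 − 2r.
- Error part (mean time 0.35, Sxx 0.6766): slope 0.1/0.6766 = 0.1478; intercept 0.0381; covariance −0.0517.
- Example, r = 0.45: slope variance 0.9 + 0.1478 = 1.0478, and SE = √(2 × 1.0478/157) = 0.116. ρ² = 0.5017²/(0.9381 × 1.0478) = 0.256, so the excess is 1/0.744 − 1 = 34%.

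Power is for a 0.34 SD difference accrued by 16 weeks, Φ(0.34/SE − 1.96).

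| r | SE as listed | SE, common baseline | Excess variance | Power as listed | Power, common baseline |
|---|---|---|---|---|---|
| 0.3 | 0.131 | 0.107 | 51% | 74% | 89% |
| 0.45 | 0.116 | 0.100 | 34% | 84% | 93% |
| 0.6 | 0.098 | 0.089 | 21% | 94% | 97% |
| 0.7 | 0.084 | 0.078 | 14% | 98% | 99% |

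**Kilogram scale (assumed).** SD rises from 0.45 to 0.80 and measurement variance is 0.01. For r = 0.3, slope variance is 0.8225 − 0.72 × 0.3 + 0.0148 = 0.6213, covariance is 0.36 × 0.3 − 0.1925 − 0.0052 = −0.0897, and intercept variance is 0.1963. So ρ² = 0.0897²/(0.1963 × 0.6213) = 0.066 and the excess is 7%. For r = 0.45, 0.6 and 0.7 it is 1%, 0.4% and 5%. Taking the SDs as free of measurement error raises the 7% to 8%. A smaller rise, to SD 0.70, gives 12% at r = 0.3. Power (SD rising to 0.80) is 86, 92, 97 and 99% as listed, against 89, 92, 97 and 99%.

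**Simulation checks.**

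- Five visits, REML, r = 0.45: mean SE 0.1146 with or without the level covariate, 0.0983 with a common intercept.
- Weeks 1, 3, 8 and 16, generalised least squares, 250 trials: estimates with and without the level covariate differed by at most 6 × 10⁻¹⁶. The empirical SD was 0.120 for both, and 0.107 with early weight by time.
- The same with 10% missing at week 16: 0.131, 0.131 and 0.114. All three estimators agreed on average.

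**The early-weight-by-time route.** Here variance falls by the factor 1 − corr(1-week weight, slope)². On weeks 1-16 with constant SD and correlations of 0.3 to 0.7, the SE falls by 18 to 8% if correlation decays with time and by 10 to 4% if it is equal at all lags. On the kilogram scale it falls by 0 to 6%.

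**The case against.** The strongest reply is that the sentence lists variables, not model terms. Arm-by-time is unlisted too, and nobody doubts that it is meant. In a hierarchical model an infant-level covariate may enter the intercept equation, the slope equation or both. Nor is it certain that the same weight is outcome and covariate: the nursery weight could be the covariate and the home visits the outcomes. This stands as far as it goes. A reader might infer that the plan definitely puts one measurement on both sides and definitely omits the slope term, but the documents do not settle either. The nursery-weight reading does not rescue a level-only term, however, because the algebra never requires the covariate to be on the curve.

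The size is also open. Every weight outcome named under Aim 1 is a z-score or percentile, which favours the z-score figures. But the growth-curve paragraph speaks only of weight, and in kilograms the loss nearly disappears. Even on the z-score scale, power as listed is 84% or more at three of the four correlations.

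Finally, this is not the powered endpoint, and it is not the only test of slower gain: the rapid-gain GEE and the conditional weight gain scores address it too. That also stands.

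**Conclusion.** The point holds as a matter of precision in one Aim 1 analysis. On its natural reading the rate test is unadjusted for early weight. The excess variance is about 14 to 51% on a z-score scale and about 0 to 8% on a kilogram scale with SD rising from 0.45 to 0.80 (up to 12% if it rises only to 0.70). These figures rest on assumed correlations, SDs, measurement error and a linear random-slope model, none of which the plan supplies.

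Three stronger conclusions are tempting and unsupported:

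- **That the rate estimate is biased or its type 1 error wrong.** It is neither. On the z-score scale a chance birth imbalance of 0.1 SD moves the estimate by about (1 − r) × 0.1, or 0.03 to 0.07 SD, but that variation is already in the standard error.
- **That the trial's primary comparison is weakened.** The 16-week BMI z model already adjusts for 1-week weight.
- **That Aim 1's slower-gain hypothesis depends on this model alone.** Two other analyses examine it.

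The change is still worth making: in these calculations the better specification never loses precision, and it uses weights the trial already collects.

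**What to change.** In section 7.a, state the weight scale, which early weight is meant, which visits form the outcome series, and that arm-by-time is the test. Then choose one of two specifications:

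1. Treat the pre-intervention weights as outcomes only, fit a baseline mean common to both arms (no arm main effect), keep gestational age as a covariate and remove early weight from the covariates. Randomisation at 7-10 days justifies a common mean at birth.
2. Keep early weight as a covariate, add early weight by time, and start the outcome series after that weight. This is a close alternative, not an identical one.

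The cost is a few lines of analysis text and no new data. Option 1 also needs a sentence in the report explaining why the arms share a baseline mean.

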## 1. Objectives

*Describe the purpose, specific aims, and hypothesis:*

Rapid weight gain in infancy is a risk factor for obesity and comorbidities later in the lifespan. This project is designed to test whether teaching mothers prompt, contingent, developmentally appropriate responsive parenting skills to soothe infants and promote adequate sleep can reduce rapid weight gain among African American infants living in the rural South. **Specific Aim 1: To assess the effects of responsive parenting, focused on infant sleep and soothing, on infant weight and reducing rapid weight gain from birth to 16 weeks among African American infants.** We hypothesize that infants in the sleep/soothe condition will have lower weight outcomes (i.e., BMI z scores, weight-for-length z scores, weight-for-age z scores) at age 16 weeks and gain weight more slowly compared to infants in a safety control condition. We consider whether weight-related factors (e.g., maternal pre-pregnancy BMI, gestational weight gain, intent to breast or formula feed, maternal smoking) moderate intervention effects. **Specific Aim 2: To assess effects of responsive parenting on parental and infant behaviors, and whether these mediate effects on infant growth.** We hypothesize that compared with control parents, parents in the sleep/soothe condition will show increases in responsive parenting, parenting self-efficacy, and the use of alternatives to feeding to soothe (white noise, pacifier, etc.), and decreases in feeding to soothe. Over time, infants in this condition will have longer sleep bouts and fewer feedings. These outcomes will be linked to healthier patterns of weight gain from birth to age 16 weeks, fully accounting for group differences. **Specific Aim 3: To examine moderation of intervention effects by individual and contextual factors.** We examine whether individual and contextual factors common among African American mothers moderate the effectiveness of the sleep/soothe intervention, informing development of future multi-component programs.

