### Enrollment at AU Hospital Newborn Nursery (after delivery, Recruitment Coordinator):

1. Obtain maternal informed consent for mother-baby dyad
2. Obtain paternal informed consent for his own participation
3. Obtain selected demographic information (race, maternal age, gestational age, weight at delivery and (self-reported) pre-pregnancy weight) from the AU medical record system
4. Complete enrollment data collection forms
  - a. Chart abstraction form (coordinator completed)
  - b. Contact form
5. Measure weight (kg) and height (cm) of mothers and fathers (if father not present, will attempt to measure at subsequent visit)
6. Measure infant anthropometry: length (cm), weight (g), head circumference (cm), and mid-thigh circumference (cm).
7. Schedule the first research visit at the home for 1 week postpartum
8. Provide participants with overview of study safety guidelines

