### Home Visit 1: (Home, 7-10 days postpartum, Community Research Associate (CRA))

1. Randomize and provide appropriate introductory materials (intervention or control) to mother-infant dyads
2. Complete questionnaire measures
3. Measure infant weight and length
4. Measure maternal weight
5. Measure paternal weight

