### Home Visit 2: (Home, 3 weeks, CRA)

1. Deliver intervention or control group program
2. Complete questionnaire measures
3. Measure infant weight and length
4. Measure maternal weight
5. Measure paternal weight

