| 
age z-score > +0.67, as described by Ong and Loos. This increase corresponds to crossing adjacent major centile lines on the standard CDC growth charts. The analysis for these rapid weight gain scores will be a repeated measures analysis, assessing the intervention effects on rapid weight gain scores from age 3 weeks up to age 16 weeks. The analysis will use generalized estimating equations (GEE) with a logit link, an extension of logistic regression which allows for repeated measurements on binary data, and will include infant weight adjusted for gestational age as a covariate. Because it is unlikely that within an 16-week period we will have many infants who meet the criteria for rapid weight gain based on the upward percentile crossing approach, we will also calculate conditional weight gain scores (CWG) following the method of Griffiths and colleagues, as described in our recent work.
 
Specific Aim 2: The Effects of Sleep SAAF on Parental and Infant Behaviors that Mediate Effects on Infant Growth. In Specific Aim 2 the primary outcomes are parental behaviors (parental self-efficacy, sleep/soothing practices, feeding practices, family chaos) and infant behaviors (sleep, soothing, and feeding) targeted by the intervention that may mediate effects on infant growth. We examine these effects in several steps.
 
First, we will examine differences between the Sleep SAAF and control groups in these outcomes at two time points post-intervention (8- and 16- weeks postpartum) using the linear mixed-effects model described above. The linear mixed-effects model will include intervention group and infant weight adjusted for gestational age. These analyses will test whether the Sleep SAAF group and the control group differ in these behaviors post-intervention and will be used to identify variables for the formal test of mediation.
 
Second, we will examine whether parent and infant behaviors mediate infant weight outcomes. We will test these hypotheses using structural equation modeling (SEM). The first step in demonstrating mediation is to establish the effects on mediating and distal outcomes, as we described above. We then specify mediators as indirect effects in a path model. Intervention condition will be dummy coded and specified as a predictor of infant and parental behaviors, which in turn predict infant weight and weight gain. The significance of the mediating process will be tested using the Sobel or bootstrapping methods.
 
Specific Aim 3: Moderation of Intervention Effects by Individual and Contextual Factors. In Specific Aim 3 we consider whether individual (depressive symptoms) and contextual (socioeconomic stressors, race-based stressors, romantic relationship characteristics, coparent relationship characteristics, social support) factors at 1 week postpartum moderate program effects. These factors will be included in the analyses described above to determine whether they moderate intervention effects on weight outcomes (Specific Aim 1) and parental and infant behaviors (Specific Aim 2).
 
As an exploratory analysis, we will also evaluate whether the individual and relationship variables differ between the Sleep SAAF group and the control group at 16 weeks postpartum. Doing so will allow us to examine whether improving infant sleep and soothing has secondary benefits for mothers' individual and relationship functioning.
 |                                         |

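### The additional rapid-weight-gain test appears to start from the 3-week weight, which is taken after randomisation and does not match Aim 1's birth-to-16-week window; the reference weight should be named and moved

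*Supplement*

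**What the plan says.** All references are to the latest protocol version in the Supplement.

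- **Aim (Section 1, Specific Aim 1).** The aim includes "reducing rapid weight gain from birth to 16 weeks among African American infants".
- **Randomisation (Section 6.a, Home Visit 1, 7-10 days postpartum).** The first listed task is "Randomize and provide appropriate introductory materials (intervention or control) to mother-infant dyads". The infant is also weighed at this visit.
- **First programme session (Section 6.a, Home Visit 2, 3 weeks).** The programme is delivered and the infant is weighed. Section 6.b confirms two sessions, at 3 and 8 weeks.
- **Rapid weight gain (Section 7.a, Specific Aim 1).** As an additional test, "weight gain z-scores will be calculated for each measurement subsequent to the first intervention session at age 3 weeks (8 weeks and 16 weeks"). Rapid gain is a rise in weight-for-age z of more than 0.67. It is analysed by GEE with a logit link, "assessing the intervention effects on rapid weight gain scores from age 3 weeks up to age 16 weeks".
- **Neighbouring analyses (Section 7.a).** The comparison of BMI z at 16 weeks adjusts for 1-week weight. The growth-curve model runs from birth to 16 weeks.
- **Earlier weights.** The nursery enrolment list includes "Measure infant anthropometry: length (cm), weight (g), head circumference (cm), and mid-thigh circumference (cm"). The Home Visit 1 list includes "Measure infant weight and length".

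**The concern.** A change score in a randomised trial should start from a value that assignment cannot have influenced. If the +0.67 rule is applied to change from week 3, its starting value is measured after families have been assigned and given arm-specific materials.

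Suppose those materials slow weight gain at all between the 1-week and 3-week visits. Treated infants then start from a lower z, and a later rise of more than 0.67 becomes easier for them to reach. Early benefit is taken out of the contrast.

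Separately, the window is not the one Aim 1 states or the one the growth-curve model uses, and no reason is given. An infant who gains rapidly before week 3 starts from an already raised z and may never be counted.

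The outcome deserves a clean definition. It is the one that directly carries the rapid-gain wording of Aim 1. It also remains computable at the no-contact 16-week visits offered to 24 dyads (Section 6.a), where weight is taken but length is not.

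**Working it through.** The plan gives no rate of rapid weight gain and no SD of z change, so there is no planned figure to reproduce. The check is calendar arithmetic, followed by an illustration on assumed inputs.

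**Step 1. Timing.** Inputs from Section 6.a: randomisation at day 7-10, Home Visit 2 at 3 weeks (day 21), final visit at 16 weeks (day 112).

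| Quantity | Calculation | Result |
|---|---|---|
| Randomisation to 3-week weight | 21 − 10 to 21 − 7 | 11 to 14 days |
| Aim 1 window | 112 − 0 | 112 days |
| Window from week 3 | 112 − 21 | 91 days |
| Share of Aim 1 window left out | 21 / 112 | 18.75% |
| Window from randomisation | 112 − 10 to 112 − 7 | 102 to 105 days |
| Share of post-randomisation time left out | 11/102 to 14/105 | 10.8% to 13.3% |

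Of the 21 omitted days, 7-10 precede randomisation, so gain in those days cannot be due to assignment.

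**Step 2. Share of effect absorbed.** This depends on how the effect builds up, which the documents do not say. If it builds evenly from randomisation, 10.8% to 13.3% is in the 3-week weight. If nothing happens before the first session, 0%. If it is front-loaded, more.

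**Step 3. Illustration for the binary outcome.** Every input here is an assumption: z change is normal with SD 0.7, control mean change is +0.2, and the total programme effect is −0.2 z. Risk = 1 − Φ((0.67 − mean)/SD).

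- Control: 1 − Φ(0.47/0.7) = 25.1%.
- Treated, pre-randomisation start (mean 0.0): 1 − Φ(0.67/0.7) = 16.9%. Difference 8.2 points.
- Treated, 3-week start: the mean becomes e, the part of the effect already present by week 3.

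| Part of effect present by week 3 (e) | Difference |
|---|---|
| 0 | 8.2 points |
| 0.022 to 0.027 (even build-up: 0.2 × 10.8% to 13.3%) | 7.4 to 7.2 points |
| 0.05 (a quarter of the effect) | 6.3 points |
| 0.10 (half the effect) | 4.3 points |

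Even build-up costs about 1 percentage point. The last row puts half of the total effect before any programme session, which is an extreme case.

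Two limits apply. A control risk near 25% sits awkwardly with Section 7.a's own expectation that few infants will meet the rule. The same SD and control mean are also used for both windows, although their lengths differ.

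**Step 4. Does the covariate repair it?** The GEE adjusts for infant weight adjusted for gestational age, with no age of measurement given. Even a 1-week weight in that place would not restore an effect already subtracted through a 3-week starting value.

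**The case against.** - **The reference weight is not named.** Section 7.a says at which visits scores are calculated and what span the model covers, but not which weight is subtracted. This stands: the 3-week start is an inference, though the natural one. If another weight was meant, the definition is incomplete and the same edit is needed.
- **It is a supplementary outcome.** This stands. A reader might infer that Aim 1's gain over 16 weeks goes untested. It does not: the primary outcome is BMI z at 16 weeks, adjusted for 1-week weight, and the growth-curve model covers birth to 16 weeks.
- **The bias is conditional.** A reader might infer that the test is shown to be biased, or that it abandons intention-to-treat. The documents support neither. Only introductory materials, whose content is not described, precede week 3. If they leave weight unchanged, no effect is lost. The arms compared are still the randomised ones, and gain after the first session is a narrower question that may have been intended. What remains is that this question is not the one in Aim 1, and that the starting value is open to influence by arm for no stated benefit.
- **A birth start has its own cost.** It adds 7-10 days of pre-randomisation change, and extra variance shrinks a thresholded contrast. In the illustration, raising the SD from 0.7 to 0.9 cuts the difference from 8.2 to 7.2 points, about the same as the even build-up loss. This stands, and it is why the 1-week weight is an equally defensible start.

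**Conclusion.** The point holds in limited form. On the natural reading, the additional rapid-weight-gain test starts from a weight taken 11-14 days after randomisation and arm-specific contact, and it covers 91 of the 112 days in Aim 1. Any programme effect before week 3 would dilute this contrast.

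The amount cannot be determined from the documents and is probably small: about 11-13% of the effect under even build-up, or roughly 1 percentage point on the assumed inputs, and nil if the introductory materials do not change weight. The mismatch with Aim 1's window does not depend on any of these assumptions. The reference for the conditional weight gain score is also unstated, so the same question arises there. No primary conclusion depends on this outcome.

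**What to change.** In Section 7.a, Specific Aim 1:

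1. Name the reference weight for the +0.67 rule and for the conditional weight gain score, and make it one measured before or at randomisation. Two choices are available:
   - the nursery enrolment weight, which matches Aim 1's window. Say whether this is the coordinator's measurement or the delivery weight from the chart (Section 4), since both are collected;
   - the weight from the 1-week randomisation visit, which matches the covariate already used in the 16-week model.
2. Use the one not chosen as a sensitivity analysis, and do not use the 3-week weight as the starting point.
3. Make the stated window agree with Aim 1. If the 1-week weight is chosen, say that for this outcome the window runs from randomisation to 16 weeks.
4. State the age of the weight covariate in the GEE.

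The cost is analysis wording. Both weights are already scheduled, and sample size and power are unchanged. The one downside is that an enrolment start brings in 7-10 days of pre-randomisation change, which adds noise but no bias.
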